**Background**

Subjective cognitive impairment refers to self-reported deterioration in cognitive performance, which is not identified objectively, by means of neuropsychological testing. Recent epidemiological evidence suggests that elderly with subjective cognitive decline, are at a heightened risk of developing dementia. Additionally, it has been reported that this population group has a relatively greater prevalence of biomarkers for amyloidosis, as well as existence of neuro-degeneration. Nonetheless, Alzheimer's disease is not the cardinal factor contributing to subjective cognitive impairment, and multiple other conditions are typically associated with subjective memory complaints, particularly, some psychiatric disorders and normal process of aging.

**Aim**

To study the effect of multimodal intervention, including cognitive training using RehaCom software, dietary counselling, and physiotherapy on improvement of cognitive function and cognitive performance in elderly, diagnosed with subjective cognitive impairment in community settings and out-patient clinics.

**Methods**

**Study Design**

A randomised controlled trial would be carried out by recruiting elderly visiting the out-patient-clinic. Subjects will be randomized 1:1:1:1 to receive either computer based cognitive therapy (CBCT) based on a Germen software Rheacom, CBCT+ diet which will be created after modification of Mediterranean diet or CBCT+Diet+ Exercise regime (which will be created by experts in the field of Physiotherapy) and the control group. The intervention group will receive 6 months of intervention to have 40-44 sessions, of 40 minutes duration and the control group brain stimulating activities such as sudoku, mental maths, and learning music and new skills.

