The exercise therapy treatment group will undergo training using Short Physical Performance Battery which comprises of balance, gait speed, and chair stand tests. Each training session will last for a minimum of sixty minutes. Balance tests such as, side-by-side stand, semi-tandem stand, tandem stand will be carried out. Moreover, gait speed testing will be carried out to assess abnormalities or deviations in normal gait pattern. Chair stand tests will also be conducted to assess leg muscle strength. Furthermore, subjects will undergo resistance training exercises involving shoulder front press, shoulder side raises, biceps curls, triceps extension, hams curls, dynamic quads, supine SLR, wall slides, and abdominal curls for three days in a week and this treatment will continue for a period of six months. During the first month of exercise training, subjects will be asked to perform (8-15) × 2 repetitions with a maximum load of 40-50% RM and the repetitions will increase to 20 × (1-3) with maximum load of 70-80% RM.

The dietary intervention will be customized from FINGER trial for Indian population in a small sample.

Then the customized diet plan focusing on increasing consumption of foods rich in omega-3 fatty acids such as flaxseeds, flaxseed oil, walnuts, mustard oil, soybean oil, roasted soybeans etc.

At baseline, patients will be assessed using the Mini Nutritional Assessment (MNA) for determining their nutritional risk level. A dietary profile questionnaire will also be administered to elderly which will gather information on their meal and snacking patterns, oral health problems, intake of omega-3 dense food items, and quantity and quality of cooking oil used in their household. Food frequency questionnaire will be used to collect information on the frequency of foods regularly consumed by the elderly subjects in the past six months.

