**Analysis Plan**

Data will be entered and analyzed using STATA software. Neuropsychological Test Battery (NTB) total score and the z-scores for executive functioning, processing speed, and memory will be calculated. For computing the NTB total score, at least 8/14 NTB components will be needed; at least 3/5 test scores for the executive functioning domain, 3/6 test scores for the memory domain, and 2/3 test scores for evaluating processing speed. Mixed-model repeated-measures analyses having a maximum likelihood estimation will be used to analyze changes in cognitive performance as a function of randomization group (dichotomous variable coded as 0 for control and 1 for intervention), time (continuous variable coded as 0 for baseline, 6-month visit, characteristic, and group × time × characteristic interaction. The characteristics will be either dichotomous (sex, presence of nutritional risk, and deterioration in quality of life) which will be dichotomized depending on the median value) or continuous variables (age, education level, scores on the following scales: MMSE, Mini-Cog, BADL, IADL, GDS-15, SF-36, and MNA). Log-transformation will be appropriately applied to the skewed continuous variables.

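### The control's exposure is neither specified nor recorded, and the 0/1 group term makes the planned contrast mix training content with exposure and leaves diet and exercise effects unattributable

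*Protocol*

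**What the plan says.** The Protocol's Aim is "To study the effect of multimodal intervention, including cognitive training using RehaCom software, dietary counselling, and physiotherapy on improvement of cognitive function". It names no comparator.

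Study Design randomises 1:1:1:1 to four arms: CBCT (the RehaCom computer training), CBCT+diet, CBCT+diet+exercise, and control. For the trained side it states: "The intervention group will receive 6 months of intervention to have 40-44 sessions, of 40 minutes duration". For the other side it states only "the control group brain stimulating activities such as sudoku, mental maths, and learning music and new skills".

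For the exercise component, the Intervention section says "Each training session will last for a minimum of sixty minutes" and, of the resistance exercises, "for three days in a week and this treatment will continue for a period of six months".

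The primary outcome is the change in PGI Memory Scale total score at six months (Outcomes). The Intervention section lists that scale's subtests, among them attention and concentration, recall and retention.

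The Analysis Plan fits a mixed repeated-measures model in which randomisation group is a "dichotomous variable coded as 0 for control and 1 for intervention". No other group term is written.

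**The concern.** The protocol puts a number and a length on the sessions of the trained arms and only examples on the control. No section gives the control a number, length or frequency of activity, and none records how much brain-stimulating activity is done in any arm. Mental maths and learning new skills could plausibly exercise functions that the PGI scale scores, so the amount done matters to the size of the difference.

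Two readings would then be hard to tell apart. A better result in the trained arms could come from the content of the training or from simply doing more. A small difference could mean that the training does little, or that the controls did a good deal of something similar. In addition, the trial pays for two arms whose purpose can only be to separate diet and exercise from computer training, yet the written group term does not use them.

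**Working it through.** **1. The protocol's own figure.** Sample Size: 15 per arm with 10% dropout gives 15 / 0.9 = 16.7, rounded up to 17; 17 x 4 = 68. This reproduces and is not in dispute. No SD, effect size, alpha or power is stated.

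**2. Exposure by arm, from the stated schedules.**
- Computer training (Study Design): 40 x 40 / 60 = 26.7 h to 44 x 40 / 60 = 29.3 h.
- Exercise (Intervention), if the sixty-minute minimum is joined to three days a week over 26 weeks: 26 x 3 = 78 sessions, at least 78 h. If this is additional to the computer sessions, the third arm has at least 78 + 26.7 = 104.7 h to 78 + 29.3 = 107.3 h.
- Control: not computable.

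The exercise total is one reading. The sixty minutes stands beside the physical performance battery and the three days beside the resistance exercises. Nor does the text say how 78 exercise occasions relate to 40-44 sessions of 40 minutes.

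**3. What the 0/1 term estimates.** Let c = CBCT minus control, d = the increment from adding diet, e = the increment from then adding exercise. The three trained arms differ from control by c, c+d and c+d+e. With equal arms, pooling them gives

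[c + (c+d) + (c+d+e)] / 3 = c + (2/3)d + (1/3)e.

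A pooled difference of 0.5 SD is then equally compatible with c = 0.5, d = e = 0; with c = 0, d = 0.75, e = 0; or with c = d = 0, e = 1.5. If the coding instead means each trained arm against control in turn, the contrasts are c, c+d and c+d+e. Neither d nor e is then estimated by any planned contrast, and c, with its unknown exposure difference, is in all of them.

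**4. What the available contrasts give.** (CBCT+diet) - CBCT = d, and (CBCT+diet+exercise) - (CBCT+diet) = e. The control drops out of both. Only c and the whole-package difference c+d+e depend on what the controls did.

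**5. Illustration of scale (assumed effects; two-sample t test, two-sided 5%, SD 1, noncentral t).**
- *Exposure alone produces a difference of 0.2 / 0.3 / 0.5 SD.* The chance of a significant result is 8% / 12% / 26% at 15 v 15, and 10% / 17% / 38% at 45 v 15.
- *Control activities deliver 0 / 25% / 50% of a true 0.8 SD effect.* The difference becomes 0.8 / 0.6 / 0.4 SD, and power at 15 v 15 is 56% / 35% / 18%.

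The first row is power to detect a real difference that might then be credited to content. It is not a type I error rate.

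**6. Price of separate contrasts.** The standard error in SD units, without baseline adjustment, is sqrt(2/15) = 0.365 for 15 v 15, against sqrt(1/45 + 1/15) = 0.298 for 45 v 15.

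**The case against.** The strongest reply is that the comparator is openly an active one. This is a legitimate choice, and it helps to separate specific training content from general mental activity. A smaller difference against such a control is a property of the question asked, not a bias, and ordinary hobbies in the trained arms are no fault. All of this stands. What it does not answer is how much activity the comparison is made against.

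A reader might infer that the Aim promises a comparison with no treatment and that the control breaks the promise. The Aim names no comparator, so it implies none. A reader might also infer that neither a positive nor a null result could answer the Aim. That goes too far: the randomised arms allow contrasts that isolate diet and exercise whatever the control does, and the control contrast remains a valid comparison with brain-stimulating activities. Nor does the text support a claim that staff contact favours the trained arms, or that the control activities are self-directed; supervision is not described for the control, and staff contact time is not stated for any arm.

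It is also fair to say that this is a pilot sized by feasibility, and that at 15 per arm power is only 56% even for 0.8 SD against an inert control. A null result would be inconclusive mainly because of size. This limits the consequence but does not remove it: Aim and Outcomes are written in terms of efficacy, and a later analysis plan can redefine contrasts but cannot recover activity data that were never collected.

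**Conclusion.** The point holds in a limited form. As written, the planned contrast with control combines the content of training with a difference in exposure that is unspecified on one side and recorded on neither. The 0/1 group term also leaves no planned contrast that attributes an effect to diet or to exercise.

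The algebra in step 3 assumes only equal arms; how many hours separate the arms is unknown, because control time is not stated. The percentages in step 5 show direction and plausible scale only. They rest on assumed effects and on a t test in place of the planned mixed model, and the 45 v 15 figures rest on the pooled reading of the coding. No stated number in the protocol is shown to be wrong. The change is worth making because half of it is free and the other half cannot be done after the trial.

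**What to change.** - **Group term.** Replace the 0/1 variable with the four randomised arms. Use CBCT+diet v CBCT for diet, CBCT+diet+exercise v CBCT+diet for added exercise, and CBCT+diet+exercise v control for the whole package. This costs only wording and some precision (standard error 0.365 against 0.298 SD), and the intervals should be reported as those of a pilot.
- **Exposure record.** Use one short diary of minutes spent on brain-stimulating activities in all four arms, and report it by arm beside the primary result. The cost is one simple form for 68 participants and a small burden on them. The diary describes exposure; because exposure arises after randomisation, it does not by itself correct the contrast.
- **Conclusions.** Word any statement from the control contrast as an effect compared with brain-stimulating activities.
- **Reconciliation.** The sponsor should reconcile the session number and length in Study Design with the exercise schedule in Intervention, and state the exposure intended for the control. Which schedule applies is for the sponsor to settle.

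No additional participants are needed.

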**Study Population**

Inclusion criteria are as follows: all consenting elderly subjects visiting the out-patient-clinic of AIIMS having SCI, aged >60 years. Both elderly men and women will provide written or verbal consent to participate in the trials.

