**Intervention**

The group imparted with computer-based customized training using RehaCom software will be assessed using Neuropsychological Test Battery (NTB) including, PGI- Memory Scale, Wisconsin Card Sorting Test, Stroop Color and Word Test. Stroop Color and Word Test will assess the relative speed of reading the names of colors and identifying the colors correctly that are printed in another color. It comprises of an interference component because it requires the participant to exhibit a reading response. The advantage of using this test is that it measures the ease with which a person can shift his perceptual set to adapt to changing demands, and to inhibit the usual response from interfering with the unusual one. This test is a measure of two essential characteristics: cognitive flexibility and response inhibition. Moreover, the PGI memory scale will be used to measure verbal and nonverbal memory. The ten sub-tests measure different memory domains such as, remote memory, recent memory, mental balance, attention and concentration, delayed recall, immediate recall, retention for similar pairs, retention for dissimilar pairs, visual retention, and recognition. Furthermore, cognitive training will include assessment of abstract reasoning and mental flexibility using the Wisconsin Card Sorting Test. The subjects can classify cards according to the color, shape of its symbols, or the number of the shapes shown on each card. With a change in the classification rule every 10 cards, it is expected that once the participant has figured out the rule, he/she will start making mistakes with an alteration in rules. This task fundamentally measures how well people can adapt to the changing rules.

Comprehensive geriatric assessment will be carried out using the Charlson Comorbidity Index, the Barthel ADL Index, IADL Scale, the Kuppuswamy scale for socio-economic status, GDS-15 for assessment of depressive symptoms, Mini-Cog for cognitive functioning, and ICIQ for determining the presence of urinary continence in subjects.

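### No exclusion or exercise-safety criterion is stated before 1:1:1:1 randomisation, although one arm in four does six months of resistance training rising to a maximum of 70-80% RM

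*Protocol*

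**What the plan says.** **Entry.** The Study Population section of the protocol admits "all consenting elderly subjects visiting the out-patient-clinic of AIIMS having SCI, aged >60 years" and adds only that men and women both give written or verbal consent. The Aim describes the target group as "elderly, diagnosed with subjective cognitive impairment in community settings and out-patient clinics". The word for diagnosis there narrows entry on the cognitive side, not the physical side.

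**Allocation.** Study Design randomises equally to four groups: computer-based cognitive therapy, the same plus diet, the same plus diet and exercise, and control. Sample Size puts 17 people in each, 68 in all.

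**Exercise.** According to Intervention, "The exercise therapy treatment group will undergo training using Short Physical Performance Battery which comprises of balance, gait speed, and chair stand tests", and "Each training session will last for a minimum of sixty minutes". Nine resistance exercises follow, three days a week for six months. The load ceiling is 40-50% RM in the first month and later 70-80% RM.

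**Assessment and safety.** Intervention also says: "Comprehensive geriatric assessment will be carried out using the Charlson Comorbidity Index, the Barthel ADL Index, IADL Scale", followed by four further scales. Outcomes provides for recording adverse events, with musculoskeletal pain and injury among the examples, and for an external safety committee that reviews safety through the study.

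**The concern.** The entry rule is a positive one: it takes everyone who meets its conditions. It is therefore more than a missing detail. If staff follow it exactly, an older out-patient who should not lift loads is eligible, and a clinician who turns that person away departs from the protocol.

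At stake is avoidable physical harm in people over 60. The protocol itself foresees musculoskeletal pain and injury as adverse events, yet plans no step at entry to keep people at high risk of them out of the exercise arm. Under a single four-way randomisation, everyone randomised has to be able to accept any of the four arms. That makes fitness for the most demanding arm an entry question.

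**Working it through.** **1. Size of the exercise arm** (Sample Size, Study Design)
- Plan's own figure: 15 / (1 - 0.10) = 16.67, rounded up to 17 per arm; 4 × 17 = 68. Both match the protocol.
- Share assigned to exercise: 17 / 68 = 25%.
- Places without exercise: 68 - 17 = 51.

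**2. What that arm does** (Intervention)
- First month: 8 × 2 = 16 to 15 × 2 = 30 repetitions, at no more than 40-50% RM.
- Later: 20 × 1 = 20 to 20 × 3 = 60 repetitions, at no more than 70-80% RM.
- Number of sessions, taking six months as 26 weeks: 3 × 26 = 78, each of at least 60 minutes.
- Study Design gives "40-44 sessions, of 40 minutes duration" for the intervention. That does not fit sessions of 60 minutes or more, so it is read here as the cognitive training. If it governed the exercise too, the count would be 40-44. The point holds under either count.

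**3. Does anything in the protocol decide who may be randomised on physical grounds?**

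| Element | Section | Decides entry on fitness? |
|---|---|---|
| Consent, clinic attendance, SCI, age over 60 (4 conditions) | Study Population | No; none concerns physical fitness |
| Diagnosis of SCI | Aim | No; cognitive only |
| Charlson, Barthel, IADL, Kuppuswamy, GDS-15, Mini-Cog, ICIQ (7 instruments) | Intervention | No stated role in entry; no timing, cut-off or purpose given |
| Physical performance battery | Intervention | No; named only for the exercise group, and no rule acts on its result |
| Regime designed by physiotherapy experts, load set as % RM, lighter first month | Study Design, Intervention | No; these shape the dose for those assigned |
| Adverse-event recording, safety committee | Outcomes | No stated role in entry |

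**4. What is already available.** Outcomes measures change in Barthel and Lawton scores, which implies baseline values, and the Analysis Plan lists BADL and IADL among participant characteristics. So part of the information for a fitness judgement is planned. What is missing is a rule that uses it before allocation.

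**The case against.** The strongest reply is that safety needs a check before someone lifts a load, not before randomisation, and that the physical performance battery sits in exactly the arm at risk. It tests balance, gait and leg strength, and the protocol introduces the resistance work after it. The exposure is also bounded: loads are ceilings scaled to each person's capacity, they start lower, and experts design the regime. A clearance rule inside the exercise arm would protect people without closing the 51 other places to the unfit.

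Part of this stands. The battery should be used, and the dosing does reduce risk. But the protocol states no rule that acts on the battery's result, and it words the battery as part of training, so its timing is unclear. Clearance inside one arm would also cause withdrawals or non-adherence after allocation in that arm alone, where only 17 - 15 = 2 people are allowed for as losses. A judgement before allocation avoids this.

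Four stronger readings are tempting and are not supported:
- *That no geriatric instrument is used at entry.* The text shows only that none has a stated role. The Background defines SCI by the absence of deficit on testing, so some cognitive testing before entry is implied.
- *That the safety measures act only after exposure.* That is an inference; nothing confines the committee to events after exercise begins.
- *That everyone will train at 70-80% RM.* That range is a maximum.
- *That Charlson, Barthel and IADL establish fitness for loaded exercise.* Nothing in the protocol says so, and the clinician's judgement should not rest on those three alone.

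**Conclusion.** The point holds and must be fixed. As written, a person unfit for progressive resistance exercise is eligible and has a 25% chance of being assigned to six months of it. No mitigating feature in the protocol decides who may enter.

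A reader might infer a number of people likely to be harmed, or a distortion of the PGI Memory Scale comparison. Neither follows. The protocol gives no share of unfit patients, so no probability is stated, and this is a safety point with no claim of bias in the primary result.

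The conclusion rests on the protocol text at hand. Eligibility belongs in the protocol, so an analysis plan would not be expected to supply it. Pilot status explains a small sample, not the lack of an entry safeguard.

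**What to change.** 1. Add to Study Population: *People whom the study clinician judges, before allocation, from medical history and the planned geriatric assessment (Charlson, Barthel, IADL), unable to do progressive resistance exercise safely will not be randomised.*
2. State in Intervention that this geriatric assessment is completed before randomisation.
3. State in Intervention that, in the exercise arm, the physical performance battery is done before the first loaded session and is used to set or reduce the load, not to exclude people after allocation.

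**Cost.** A short protocol amendment. No new instrument or numeric cut-off is needed, because the decision is the clinician's. The assessment has to come before randomisation, so it is also done in people who are then turned away. Results would apply to people fit for exercise, a narrower group than the Aim describes, and unfit people would lose access to the 51 places in the three arms without exercise. How many that affects cannot be derived from the document.

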**Intervention**

The group imparted with computer-based customized training using RehaCom software will be assessed using Neuropsychological Test Battery (NTB) including, PGI- Memory Scale, Wisconsin Card Sorting Test, Stroop Color and Word Test. Stroop Color and Word Test will assess the relative speed of reading the names of colors and identifying the colors correctly that are printed in another color. It comprises of an interference component because it requires the participant to exhibit a reading response. The advantage of using this test is that it measures the ease with which a person can shift his perceptual set to adapt to changing demands, and to inhibit the usual response from interfering with the unusual one. This test is a measure of two essential characteristics: cognitive flexibility and response inhibition. Moreover, the PGI memory scale will be used to measure verbal and nonverbal memory. The ten sub-tests measure different memory domains such as, remote memory, recent memory, mental balance, attention and concentration, delayed recall, immediate recall, retention for similar pairs, retention for dissimilar pairs, visual retention, and recognition. Furthermore, cognitive training will include assessment of abstract reasoning and mental flexibility using the Wisconsin Card Sorting Test. The subjects can classify cards according to the color, shape of its symbols, or the number of the shapes shown on each card. With a change in the classification rule every 10 cards, it is expected that once the participant has figured out the rule, he/she will start making mistakes with an alteration in rules. This task fundamentally measures how well people can adapt to the changing rules.

Comprehensive geriatric assessment will be carried out using the Charlson Comorbidity Index, the Barthel ADL Index, IADL Scale, the Kuppuswamy scale for socio-economic status, GDS-15 for assessment of depressive symptoms, Mini-Cog for cognitive functioning, and ICIQ for determining the presence of urinary continence in subjects.

The exercise therapy treatment group will undergo training using Short Physical Performance Battery which comprises of balance, gait speed, and chair stand tests. Each training session will last for a minimum of sixty minutes. Balance tests such as, side-by-side stand, semi-tandem stand, tandem stand will be carried out. Moreover, gait speed testing will be carried out to assess abnormalities or deviations in normal gait pattern. Chair stand tests will also be conducted to assess leg muscle strength. Furthermore, subjects will undergo resistance training exercises involving shoulder front press, shoulder side raises, biceps curls, triceps extension, hams curls, dynamic quads, supine SLR, wall slides, and abdominal curls for three days in a week and this treatment will continue for a period of six months. During the first month of exercise training, subjects will be asked to perform (8-15) × 2 repetitions with a maximum load of 40-50% RM and the repetitions will increase to 20 × (1-3) with maximum load of 70-80% RM.

The dietary intervention will be customized from FINGER trial for Indian population in a small sample.

Then the customized diet plan focusing on increasing consumption of foods rich in omega-3 fatty acids such as flaxseeds, flaxseed oil, walnuts, mustard oil, soybean oil, roasted soybeans etc.

At baseline, patients will be assessed using the Mini Nutritional Assessment (MNA) for determining their nutritional risk level. A dietary profile questionnaire will also be administered to elderly which will gather information on their meal and snacking patterns, oral health problems, intake of omega-3 dense food items, and quantity and quality of cooking oil used in their household. Food frequency questionnaire will be used to collect information on the frequency of foods regularly consumed by the elderly subjects in the past six months.

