**Outcomes**

The primary outcome will be measured after 6 months by evaluating change in cognitive performance by using PGI Memory Scale total score. Improvements in cognitive domains including executive functioning, processing speed, attention, and memory will be recorded. Secondary outcomes including change in functionality and quality of life will be measured using Barthel's ADL Index, Lawton's Scale, and SF-36 respectively. By utilization of the visual paired associates test, immediate and delayed recall, logical memory immediate and delayed recall, word list learning and delayed recall will be reassessed for noticing changes in the memory domain. Adverse events such as presence of psychological stress, musculoskeletal pain, or injury will be recorded. An external safety committee will regularly assess safety-related issues throughout the duration of the study.

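### The Intervention section gives the outcome battery only to the RehaCom-trained group and places one of its tests, the WCST, inside training, in conflict with Outcomes and Analysis Plan

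*Protocol*

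**What the plan says.** **Who is tested.** The Intervention section of the Protocol opens with "The group imparted with computer-based customized training using RehaCom software will be assessed using Neuropsychological Test Battery (NTB" and names the battery's content as "PGI- Memory Scale, Wisconsin Card Sorting Test, Stroop Color and Word Test". It has no matching sentence for the control group.

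**What training contains.** The same section says that "cognitive training will include assessment of abstract reasoning and mental flexibility using the Wisconsin Card Sorting Test". Its exercise paragraph has a similar construction: "The exercise therapy treatment group will undergo training using Short Physical Performance Battery".

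**Arms.** Study Design states "Subjects will be randomized 1:1:1:1 to receive either computer based cognitive therapy (CBCT", followed by that therapy plus diet, that therapy plus diet and exercise, and control. Controls receive "the control group brain stimulating activities such as sudoku, mental maths, and learning music and new skills".

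**Outcomes.** "The primary outcome will be measured after 6 months by evaluating change in cognitive performance by using PGI Memory Scale total score". In addition, "Improvements in cognitive domains including executive functioning, processing speed, attention, and memory will be recorded". Neither sentence is restricted to an arm.

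**Analysis Plan.** Cognitive change is modelled on randomization group, with control as 0 and intervention as 1, and on time from baseline to the 6-month visit. An NTB total and domain z-scores for executive functioning, processing speed and memory are to be calculated.

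**The concern.** Two things are run together: what is measured, and what is given as treatment.

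First, the only sentence that assigns the battery to anyone assigns it to trained participants. The battery includes the primary outcome instrument. Staff who follow that sentence literally would not test the controls, and a baseline score that was never collected cannot be recovered later.

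Second, a battery test is described as part of the training. If participants meet the WCST during training, they learn how it works. By the protocol's own account, the task depends on finding a sorting rule and coping when that rule changes. This exposure would occur in the active arms and not in control, so on the WCST score it could not be told apart from a treatment effect.

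**Working it through.** **1. The sections side by side**

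| Section | Control group tested? |
|---|---|
| Intervention | Not named; the battery goes to the RehaCom-trained group |
| Outcomes | Implied; no limit by arm |
| Analysis Plan | Required; control is the reference value in the model |

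The first row cannot be followed literally if the third is to be carried out. The phrase for the trained group is also ambiguous. It can mean the arm with cognitive therapy alone, or all three arms that contain it.

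**2. How many participants the literal reading touches**

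The Sample Size section reproduces: 15 / 0.9 = 16.7, rounded up to 17 per group, and 4 × 17 = 68. Read literally, the 17 controls have no battery. If the phrase means only the arm with cognitive therapy alone, 3 × 17 = 51 of 68 have none.

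**3. Where WCST exposure would fall**

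Cognitive therapy is in three of the four arms, and control activities name no cognitive test. Any WCST use within training therefore coincides exactly with active versus control. The PGI Memory Scale is not placed in training, so this route does not reach the primary outcome directly.

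**4. Size of a practice effect on the planned scores**

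The Analysis Plan has five executive tests (at least three needed), six memory tests and three processing-speed tests. 5 + 6 + 3 = 14, which agrees with its 14 components.

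Assumptions, none given in the protocol:
- the WCST supplies one score, and it belongs to the executive domain;
- scores are equally weighted;
- the practice gain g is 0.5 to 1.0 SD on the WCST, in trained arms only.

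With k scores averaged, the shift is g / k, in units of a single test's SD:
- executive domain, k = 5: 0.5/5 = 0.10 to 1.0/5 = 0.20;
- executive domain, k = 3: 0.5/3 = 0.17 to 1.0/3 = 0.33;
- NTB total, k = 14: 0.5/14 = 0.04 to 1.0/14 = 0.07.

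The k = 3 range would be the group shift only if everyone had just the minimum number of tests and the WCST was one of them. If the WCST supplied more than one component, the shifts would be larger.

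**5. Chance of a spurious difference on one test score**

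This is an illustration, assuming two-sided alpha 0.05, SD 1, no true effect and a normal approximation. For a practice gain b,

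P = Φ(b/SE − 1.96) + Φ(−b/SE − 1.96), with SE = √(1/n₁ + 1/n₀).

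For 15 v 15, SE = √(2/15) = 0.365. For pooled active v control, 45 v 15, SE = √(1/45 + 1/15) = 0.298.

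| b (SD) | 15 v 15 | 45 v 15 |
|---|---|---|
| 0.1 | 5.9% | 6.3% |
| 0.2 | 8.5% | 10.3% |
| 0.3 | 13.0% | 17.2% |
| 0.5 | 27.8% | 38.9% |

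These figures apply to a single test score. They do not carry over to the composites, whose SD depends on correlations that the protocol does not give.

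**The case against.** The strongest reply is that this is loose wording in one section. Outcomes sets the primary outcome for the whole trial, and the Analysis Plan cannot be run without control scores. The Intervention section also holds assessments with no arm attached, such as the comprehensive geriatric assessment and the nutritional questionnaires, so its heading does not confine testing to treated participants. This stands. A reader might infer that controls have no scheduled cognitive outcome, but the other two sections do not support that.

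A reader might also infer that trained participants rehearse the WCST throughout the 40 to 44 sessions. The protocol does not say so. It uses the word assessment, describes what the test measures, gives no frequency, and does not call the test a RehaCom module. Rehearsal is a risk that the wording permits, not a stated procedure.

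Three further limits stand. The primary outcome is not placed in training. The composites could be recalculated without the WCST, so they are not beyond repair, although the WCST score itself would be. The Short Physical Performance Battery is not among the stated outcomes or the modelled variables, so calling it training biases no stated result.

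The reply does not remove the contradiction. The one sentence that says who receives the battery names only trained participants, and the sentence about training does include a battery test. Who is tested, and what the sessions contain, are matters for the protocol. A statistical analysis plan cannot supply scores that were not collected.

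**Conclusion.** The point holds as an internal contradiction with a possible bias. The Intervention section limits the battery to the RehaCom-trained group, against Outcomes and the Analysis Plan. This part touches the primary outcome, because the battery contains the PGI Memory Scale.

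The placement of the WCST in training leaves open an exposure confined to the three active arms. It would favour them on the executive-function z-score and, more weakly, on the NTB total. Under the assumptions in the working, the shift is 0.10 to 0.20 SD for the executive domain with five tests, 0.17 to 0.33 SD at the permitted minimum of three, and 0.04 to 0.07 SD for the 14-component total. The practice gain, the weights and the number of WCST components are all assumed. If the WCST is in fact given only at the two outcome visits, in all arms alike, the differential exposure is nil.

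**What to change.** Amend the Intervention section to say that:

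- all four arms complete the same battery (PGI Memory Scale, WCST, Stroop) at baseline and at 6 months, under the same procedure;
- the WCST is an outcome test given only at those visits and is not part of the training sessions.

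Reconcile the exercise paragraph on whether the Short Physical Performance Battery is an assessment or training content. No stated outcome depends on the answer.

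The cost is a wording change. The control assessments are already presumed by the Analysis Plan, so no new visits follow from it. It should be made before enrolment, because missing baselines and unequal exposure cannot be undone. If some participants have already met the WCST in training, the executive and total scores should also be reported without it.
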